Meanwhile, it is worth noting that there is still no effective strategy developed to assess the coagulation function of surgical patients on LOAPT. Given antiplatelet medication can have a significant impact on hemostasis and coagulation, the risk of intraoperative hemorrhage and postoperative intracranial bleeding (PIB) is a major focus because they can cause fatality [1, 2]. Though the preoperative screening of coagulation function could be effective in protecting patients from developing hemorrhagic complications, those commonly used methods are not applicable to assess the coagulation function of patients on LOAPT as the antiplatelet medication mainly affects platelet function, rather than clotting factors. Notably, there are various tools, such as thromboelastogram (TEG), reported to aid medical professionals in assessing the platelet function in the cardiac surgery and intracranial traumatic injury [17, 18]. Therefore, they have a potential to assist with the development of suitable treatment strategy for SSICH patients on LOAPT.

In addition to hemorrhagic complications, ischemic complications are also a problem worthy of consideration during the management of SSICH patients on LOAPT due to the hypercoagulable state caused by discontinuing antiplatelet medications. Besides, even though patients are stable after receiving appropriate treatment, it remains debatable to resume antiplatelet treatment. Therefore, there are many SSICH patients who have a history of antiplatelet treatment still stopping antiplatelet treatment after primary hemorrhage, which makes them under high risk of ischemic complications.

According to a previous study, the outcome after spontaneous intracerebral hemorrhage is poor, and the mortality could exceed 30% [1, 19]. Nevertheless, considering a lack of clarity on the effect and safety of emergency surgery for SSICH patients on LOAPT, there is no evidence gathered to support clinical decision-making. Therefore, a prospective cohort study will be conducted to investigate the safety and effect of emergency surgery for SSICH patients on LOAPT, based on which a scientific strategy will be proposed for the selection of an appropriate treatment.

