### Thrombelastography (TEG) test and coagulation function assessment system

TEG is performed to monitor the function of platelet with the assistance of Thrombelastograph Coagulation Analyzer (TEG model 5000, Haemoscope Corporation, Niles IL, American). All parameters, including maximum amplitude (MA, mm), citric acid kaolin tracing (CK), reptilase tracing (A), aspirin tracing (AA), and clopidogrel tracing (ADP), are recorded through standard tracing. Based on MA, the rate of platelet inhibition was calculated using the formula as shown below:
$$ AA/ ADP\%=\frac{\mathrm{MA}\left(\mathrm{CK}\right)-\mathrm{MA}\left(\mathrm{A}\mathrm{A}/\mathrm{ADP}\right)}{\Big(\mathrm{MA}\left(\mathrm{CK}\right)-\mathrm{MA}\left(\mathrm{A}\right)} $$

where AA% represents the inhibition to platelet caused by aspirin, and ADP% indicates the inhibition to platelet caused by clopidogrel. Further with traditional coagulation test including bleeding time, prothrombin time, activated partial thromboplastin time, and fibrinogen as well as TEG, we plan to establish a combined coagulation function assessment system in order to assess the surgical risk facing SSICH patients on LOAPT, with the focus placed on PIB. Moreover, for the patients not on LOAPT, it is considered that these patients have normal platelet function and do not need to undergo further relative test.

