## Results

China National Clinical Research Center for Neurological Diseases will be responsible for data analysis. Sample size was calculated by using PASS (Version 15, NCSS corporation, American). All sample size calculations were performed by conducting two-sided test, *α* = 0.05 and *β* = 80% (the degree of control = 80%). In this study, two comparison groups will be established, with the primary and secondary outcomes as the focus in this study. According to our unpublished data collected from 7 participating centers in 2019, for SSICH patients on LOAPT, the total mortality was about 30% for operated patients and 45% for the patients receiving conservative treatment, with the ratio of two groups reaching about 1:1.5. Moreover, for operated SSICH patients, the incidence of PIB was about 23% for patients on LOAPT and 10% for patient not on LOAPT, with the ratio of two groups reaching about 1:2.5. With regard to the primary outcome, our sample size was calculated as 196 (196 SSICH patients on LOAPT, operation group: *n* = 78; conservation group: *n* = 118). As for the secondary outcome, the sample size was 247 (247 operated SSICH patients, LOAPT group: *n* = 70; non-LOAPT group: *n* = 177). Moreover, in order to establish the coagulation function assessment system, the area under curve was expected to be 0.7, and the sample size was set to 92 (92 operated SSICH patients on LOAPT, PIB group: *n* = 23; non-PIB group: *n* = 69). In this case, a minimum of 387 SSICH patients (includes 118 patients on LOAPT receiving conservative treatment, 92 patients on LOAPT receiving emergency surgery, and 177 patients not on LOAPT receiving emergency surgery) may be required in this study to reach our research objective. Thus, to ensure final statistics, a total of 400 patients (patients on LOAPT receiving conservative treatment, *n* = 120; patients on LOAPT receiving emergency surgery, *n* = 100; patients not on LOAPT receiving emergency surgery, *n* = 180; Fig. 1) will be recruited. In this study, 10% of patients would be lost during follow-up. Finally, we decided to recruit 450 appropriate patients.

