All statistical analyses were conducted with the assistance of SPSS (Version 22.0, IBM, American). The data was indicated as mean (x) ± standard deviation (SD) for normally distributed data, median, and interquartile range (IQR) for skewed distributed data or number (*n*) and percentage (%). In this study, two main comparative groups and an observational cohort will be established, as shown in Fig. 1. Firstly, in order to investigate the effect of emergency neurosurgery, a comparison will be performed between SSICH patients on LOAPT receiving conservative treatment and those receiving emergency neurosurgery. Secondly, in order to investigate the safety of emergency neurosurgery, a comparison will be performed between operated SSICH patients on LOAPT and those not on LOAPT. Thirdly, in order to investigate the intra/postoperative complications and the risk of ischemic disease after discontinuing antiplatelet treatment, the characteristics of SSICH patients on LOAPT will be analyzed; moreover, because the history of previous neural ischemic events or cardiac events could affect the risk of postoperative ischemic events, we would perform the subgroup analysis depending on this history to further investigate the effect of discontinuing antiplatelet treatment on the risk of ischemic disease. The difference will be compared by conducting χ^2^ test, Mann-Whitney *U* tests, or Student’s *t* tests. The independent risk factors were analyzed by logistic regression, while the factors with *p* < 0.10 in univariate analysis were entered into a multivariate logistic regression model. The result was indicated as odd ratio (OR) and 95% confident interval (CI). The receiver operating characteristic (ROC) curve analysis was performed to test the prediction value of different parameters and different methods. An area under the curve (AUC) in a ROC analysis of ≥ 0.7 is considered as a clinical utility, while *p* value of < 0.05 was treated as statistically significant.

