Another problem confusing neurosurgeon is how to assess the surgical risk of SSICH patients on LOAPT. The main surgical risk facing these patients stems from the coagulation disorder caused by antiplatelet medication [9, 11, 25]. It has been found out that there is a close association between coagulation condition and hemorrhagic complications. Notably, the common tests used in neurosurgical practice now are purposed simply to assess the coagulation function maintained by clotting factors. Nevertheless, these tests are insufficient to reveal the coagulation disorder caused by platelet function abnormality. Therefore, it is also imperative to establish a complete and applicable assessment system for SSICH patients on LOAPT. Though such tools as TEG and Verifynow were employed in previous study to assess platelet function, similar study was rarely conducted in neurosurgery. In a study conducted Holzmacher et al., the effect of platelet transfusion on prognosis in brain trauma patients was investigated, and the platelet function performed by TEG was examined [26]. Despite demonstrating that TEG can reflect the change of platelet function, this study failed in establishing the correlation between intra/postoperative complications and the result of TEG. Therefore, another crucial aim of this current study is to establish an effective and quick coagulation assessment system for SSICH patients on LOAPT, which is beneficial to neurosurgery.

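### The utility rule is an absolute AUC of at least 0.7 with no comparison with and without TEG, so it cannot show that TEG contributes beyond the routine coagulation tests

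*Protocol article*

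**What the plan says.** The case for TEG rests on what routine tests miss. The Background states that "those commonly used methods are not applicable to assess the coagulation function of patients on LOAPT", because antiplatelet drugs act on platelets and not on clotting factors. The Discussion repeats that "these tests are insufficient to reveal the coagulation disorder caused by platelet function abnormality".

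The TEG section lists bleeding time, prothrombin time, activated partial thromboplastin time, fibrinogen and TEG, and says "we plan to establish a combined coagulation function assessment system in order to assess the surgical risk", with PIB as the focus.

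The Results section sizes this part on one figure: "the area under curve was expected to be 0.7, and the sample size was set to 92", split into 23 patients with PIB and 69 without. For the analysis it says that ROC "analysis was performed to test the prediction value of different parameters and different methods" and that an AUC of 0.7 or more "is considered as a clinical utility".

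The same section plans logistic regression for independent risk factors. Factors with p < 0.10 in univariate analysis enter a multivariable model. It does not name the outcome or the candidate factors for this regression, and it does not tie the regression to the 0.7 rule.

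**The concern.** If TEG is justified by information that routine tests lack, the evidence that bears on it is what TEG adds once those tests are known. An absolute AUC does not measure that. A TEG value that only tracks the routine results inherits part of their discrimination and can reach 0.7 without adding anything. The combined system has the same weakness: it can pass 0.7 on the routine tests alone.

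What is at stake is the fourth aim. A report could describe TEG, or a system containing it, as clinically useful when tests already being done would have performed as well. A larger or validated sample would not cure this, because the rule asks whether a marker discriminates and not whether it adds.

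**Working it through.** **1. The plan's own figure.** Inputs from the Results section: two-sided test, alpha 0.05, power 80%, expected AUC 0.7, PIB incidence 23% in operated patients on antiplatelet treatment. The article gives no null AUC; 0.5 is assumed here. The Hanley–McNeil variance is

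V(A) = [A(1−A) + (n1−1)(Q1−A²) + (n0−1)(Q2−A²)] / (n1·n0), with Q1 = A/(2−A) and Q2 = 2A²/(1+A).

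The requirement is 1.96·√V(0.5) + 0.84·√V(0.7) ≤ 0.7 − 0.5 = 0.20. An incidence of 23% gives a ratio of 77/23 = 3.35 patients without PIB per patient with PIB.

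- 20 + 67 = 87: the left side is 0.205, too large.
- 21 + 71 = 92: 1.96 × 0.0721 + 0.84 × 0.0696 = 0.200, which meets the requirement.

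The total of 92 is reproduced. The printed 23/69 split corresponds to 23/92 = 25%, not 23%, but its power is similar (83–84%). So 92 is what a test of one AUC against chance needs. It was not derived from a comparison of systems with and without TEG.

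**2. Precision at 23/69.** V(0.7) = (0.21 + 22 × 0.0485 + 68 × 0.0865)/1587 = 0.00451, so SE = 0.067 and the 95% CI around an observed 0.70 is 0.57 to 0.83.

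**3. How often a redundant TEG value passes.** The article gives neither the AUC of the routine tests for PIB nor their correlation with TEG, so both are varied. Model: routine score S normal with SD 1, shifted by d = √2·Φ⁻¹(AUC) in patients with PIB; TEG = r·S + √(1−r²)·noise, so TEG carries no information beyond S. There were 3,000 simulated studies per cell at 23/69.

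| Assumed routine AUC | TEG alone ≥ 0.7, r = 0.5 / 0.7 / 0.9 | Combined score ≥ 0.7 |
|---|---|---|
| 0.60 | 1% / 3% / 5% | 10–11% |
| 0.70 | 8% / 20% / 41% | 58–59% |
| 0.72 | 11% / 27% / 51% | about 70% |
| 0.75 | 15% / 40% / 69% | 84–85% |
| 0.80 | 29% / 64% / 92% | 97–98% |

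Separate simulations of the same model differ by a few points. They gave 2–7% at 0.60, 10–53% at 0.72 and 28–91% at 0.80. The combined AUC is the apparent one, from a model fitted to the same 92 patients.

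**4. What a nested test does in the same data.** A 1-df likelihood-ratio test of TEG added to the routine score rejected in about 4–7% of these studies, close to its nominal 5%. When TEG instead carries independent information worth AUC 0.70, its power is about 81–87% (routine AUC 0.60 to 0.72).

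**5. A formal test of the AUC difference is weak here.** By the Obuchowski covariance formula at 23/69, power is 23–47% for 0.70 versus 0.80 (correlation 0.3 to 0.7) and 9–16% for 0.70 versus 0.75. Reaching 80% would need about 204–472 and 812–1,896 patients respectively.

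**The case against.** A reader might infer that TEG is judged by its own AUC and that the study's question will therefore go unanswered. The documents do not support that, for three reasons.

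- The 0.7 rule is not specific to TEG. It applies to any ROC analysis, and the sample-size paragraph attaches 0.7 to the assessment system, which is a combined one.
- TEG's increment is the rationale in the Background and Discussion. It is not a stated hypothesis. The stated aim is to establish a system, and nowhere does the article say that TEG will be recommended if its AUC reaches 0.7.
- The multivariable logistic regression could show whether TEG is associated with PIB independently of routine tests. In a simulation at 23/69 with one routine score of AUC 0.72 and the p < 0.10 entry rule, the score entered the model in 95–97% of studies. Redundant TEG was declared independent in only 2–5%, and passed both this test and the 0.7 rule in 2–3%.

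The size can also be challenged. The article argues that routine tests miss platelet dysfunction. If they predict PIB poorly, redundant TEG seldom passes, as the 0.60 row shows. The 51% at routine AUC 0.72 and correlation 0.9 is close to built in, since TEG's true AUC there is 0.70.

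Finally, an article condenses its protocol, and a nested comparison may be set out elsewhere.

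These points limit the claim but do not remove it. The regression helps only if routine tests and TEG are both candidates for PIB, if the routine tests survive the p < 0.10 screen, and if its result governs the claim. The article fixes none of these, so TEG could be non-significant after adjustment and still meet the utility rule. The point is also not a missing detail: the article states a decision rule, and that rule does not match the reason it gives for the test.

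**Conclusion.** The point holds in a limited form. The only stated criterion of clinical utility is an absolute AUC of at least 0.7. It cannot show that TEG, alone or within the combined system, contributes beyond routine tests. That the rule can be passed without any contribution from TEG needs no numerical assumption. How often this would happen does: from a few percent if routine tests are weak predictors of PIB to most studies if they are strong and closely correlated with TEG. The simulation further assumes a single, known routine score and normally distributed markers. The matter affects the fourth aim and not the mortality comparison, and it merits a change before analysis.

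**What to change.** In operated patients on long-term antiplatelet treatment, base any claim that TEG is useful on one nested comparison:

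- **Base model:** logistic regression of PIB on one prespecified score of the routine coagulation tests, kept in the model whatever its univariate p-value.
- **Extended model:** the same plus one prespecified TEG inhibition variable.
- **Test:** 1-df likelihood ratio at 5%.
- **Report:** the routine-only AUC, the combined AUC and their difference with a 95% CI. Present the difference as an estimate, since 92 patients give low power for a formal test of it.

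Keep the single-parameter ROC curves and the 0.7 threshold as description.

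The cost is one more model on data already collected. With about 21 to 23 events (92 × 0.23 = 21, or the printed 23), only one TEG variable can be tested, so fewer parameters can be claimed as useful. The article gives no weights for a routine score, so these must be fixed beforehand. Estimating them from so few events would use degrees of freedom, and the 81–87% power, which assumes a known score, should not then be relied on.

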### Ethics and public involvement

Patients or the public were not directly involved in design or conduct of the study. This study was granted approval from Institutional Review Board of Beijing Tiantan Hospital, and the research would be conducted in strict accordance with the declaration of Helsinki and Human Biomedical Research Ethical Issues. In this study, researchers are not able to use randomized controlled trials; thus, all recruited SSICH patients will not be affected by normal course of diagnosis and treatment. When SSICH patients are included, they will be followed up until 6 months after the occurrence of primary hemorrhage.

## Discussion

For the patients with SSICH, despite surgical intervention capable of saving life, the intraoperative and postoperative complications caused by an invasive procedure would lead to a secondary injury for those patients, which could result in a more catastrophic consequence, which explains why the previous evidences recommend against invasive procedures for the patients on antiplatelet medication. Over the most recent decades, however, due to the common use of antiplatelet medication, the rate of SSICH patients on LOAPT was on the increase annually, which prompts the exploration of appropriate treatment for SSICH patients on LOAPT. However, the problems we are facing now are neither appropriate treatment strategy nor assessment system of surgical risk for SSICH patients on LOAPT. At present, what confuses neurosurgeons is whether to perform emergency surgery on SSICH patients on LOAPT.

Considering that the mortality of all SSICH patients could reach as high as more than 30%, which is much higher among the patients with reduced platelet activity caused by LOAPT [19], it is essential to determine which treatment can benefit SSICH patient on LOAPT. SSICH tends to progress rapidly after primary hemorrhage, and the significant increase of intracranial pressure could put patients at high risk of developing cerebral hernia, which is a main cause of fatality [2, 20]. Though conservative treatments, known as mannitol, methylprednisolone, and hypertonic saline, may be effective in preventing patients from developing cerebral hernia, emergency surgery remains worth considering because this method can achieve quick and effective evacuation of hematoma, reduce high intracranial pressure, and prevent encephaledema-induced secondary cerebral hernia [4, 7, 21–23]. At present, the study about surgery for SSICH has yet to obtain any evidence suggesting that emergency neurosurgery can help reduce the mortality of SSICH patients on LOAPT. It is only in a study conducted by Stein et al. that the rate of in-hospital mortality was lower in the patients receiving surgery as compared to the patients receiving conservative treatment [24]. However, as this study is a retrospective study and most of the patients received only conservative treatment, the currently available data is still insufficient to support neurosurgeons in performing emergency surgery for SSICH patients on LOAPT, which explains why this study was conducted.

Another problem confusing neurosurgeon is how to assess the surgical risk of SSICH patients on LOAPT. The main surgical risk facing these patients stems from the coagulation disorder caused by antiplatelet medication [9, 11, 25]. It has been found out that there is a close association between coagulation condition and hemorrhagic complications. Notably, the common tests used in neurosurgical practice now are purposed simply to assess the coagulation function maintained by clotting factors. Nevertheless, these tests are insufficient to reveal the coagulation disorder caused by platelet function abnormality. Therefore, it is also imperative to establish a complete and applicable assessment system for SSICH patients on LOAPT. Though such tools as TEG and Verifynow were employed in previous study to assess platelet function, similar study was rarely conducted in neurosurgery. In a study conducted Holzmacher et al., the effect of platelet transfusion on prognosis in brain trauma patients was investigated, and the platelet function performed by TEG was examined [26]. Despite demonstrating that TEG can reflect the change of platelet function, this study failed in establishing the correlation between intra/postoperative complications and the result of TEG. Therefore, another crucial aim of this current study is to establish an effective and quick coagulation assessment system for SSICH patients on LOAPT, which is beneficial to neurosurgery.

The last focus of this study is ischemic complication after discontinuing antiplatelet medication. It is worth mentioning that the patients on antiplatelet medication are put at high risk of developing ischemic diseases including cardiovascular diseases and ischemic stroke. After a long period of discontinuing antiplatelet treatment, just for surgery, it is possible for these patients to develop ischemic diseases perioperatively or postoperatively [27]. This risk may be significantly higher for patients with ischemic stroke as neurosurgery could affect the cerebral blood flow and perfusion [2]. After the treatment of spontaneous intracranial hemorrhage, it is advisable to resume antiplatelet treatment. However, what confuses neurosurgeons is when and how to safely re-start antiplatelet medication. Moreover, there is currently still no relevant study reporting the incidence and risk factors of ACCE after neurosurgery in SSICH patients on LOAPT. Thus, credible evidence is needed to guide postoperative management. In this study, the patients will be followed up until 6 months after primary hemorrhage to investigate the risk of ACCE and the association between the discontinuation of antiplatelet treatment and ischemic complications. It is believed that this study will also provide an evidence to prevent SSICH patients on LOAPT from the development of ischemic complications and a basis for further investigation into the safe resumption of antiplatelet treatment in the future.

Based on our current study design, however, there remain some questions left unresolved. The first one is the indications of neurosurgery for SSICH patients on LOAPT. The second one is the effect of craniotomy, endoscopy, and minimally invasive surgery on SSICH patients on LOAPT. The third one is the advantage of different tools in assessing platelet function. The fourth one is when and how to resume antiplatelet treatment after neurosurgery. Surgical outcome and safety tend to be what neurosurgeons focus on. Despite the limitations to which our current study is subject, it is still believed that our study could provide a basis for the further exploration of appropriate treatment strategy for spontaneous intracranial hemorrhage patients on LOAPT.

